Pre-existing anaemia on admission is further exacerbated by the effects of intravenous rehydration, and small but significant intra-operative blood loss results in between one-third and two-thirds of patients receiving blood transfusions within the first few days following operation [5]. The likelihood of transfusion is related to fracture type: subtrochanteric and trochanteric fractures have the highest transfusion rates in both anaemic and nonanaemic subjects. Poor nutrition in the postoperative period is also unlikely to replenish iron stores. Surgery itself may further induce a functional iron deficiency due to humoral suppression of erythropoiesis [12]. Functional iron deficiency does not respond well to oral iron, as iron stores may be normal, and this suppresses intestinal absorption of iron. Indeed, postoperative oral iron has been shown to be of no benefit and also has a high incidence of side effects [13]. Whereas blood transfusion improves [Hb], some authors have found an association between transfusion and improved mobility [5]; others have not found this association, but found that transfusion might reduce readmission rates [14]. Infection rates may also be increased with the use of blood transfusion [15] and there are significant financial constraints with the current cost of a unit of blood in the UK around £200. A recently reported North American trial assessed the effects of liberal versus restrictive postoperative transfusion strategies following hip fracture in patients with cardiovascular risk factors [16-18]. That study found no differences in self-reported mobility or death at 60 days, though there was an increase in cardiovascular complications in the restrictive group. It would seem therefore, at this time that anaemia is a poor prognostic factor but that red cell transfusion does not necessarily alter outcome.

Alternatives to blood transfusion include reduction in blood loss in the perioperative period; stimulation of erythropoiesis with erythropoietin; and oral or intravenous iron.

Pharmacological reduction of blood loss with tranexamic acid has been assessed recently [19]. Although there was a trend to reduced transfusion requirements and reduced postoperative infections, there was also a trend towards increased thrombotic events in the tranexamic acid group and it is therefore not a recommended therapy in this group, despite being advocated for patients with multiple traumas [20].

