Erythropoietin has been used in older people to stimulate erythropoiesis. However, the side effects of erythropoietin (hypertension, risks of thrombotic events) make it unattractive in the hip fracture population and the cost of erythropoietin used in these studies is high, over £200 per patient.

Intravenous iron is an attractive therapy in this population. Intravenous iron bypasses the intestinal barrier to absorption [21] that may be seen in functional iron deficiency and stimulates erythropoiesis. The effects of i.v. iron are believed to last for around 7 days, which covers the at-risk period for patients with hip fracture. In post-partum women, who commonly have moderate blood loss during delivery, i.v. iron has been shown to have a faster effect on [Hb] than oral iron [22]. Intravenous iron is believed to be much less likely to cause adverse reactions than in the past, following changes in its pharmaceutical preparation. Iron sucrose is associated with the lowest rate of life-threatening adverse events of all the i.v. iron preparations and these are considerably lower than transfusion-related severe side effects (0.11/million versus 10/million) [23]. Four studies from a Spanish group have reported the effects of i.v. iron on transfusion requirements, mortality and outcome compared with historical controls [21]. Cuenca and colleagues [24] reported a nonsignificant reduction in transfusion rate in patients with trochanteric fractures (55% vs. 44%). A prespecified subgroup of patients with [Hb] >12 demonstrated a significant reduction in transfusion rate (41% vs. 26%). In another retrospective study, transfusion rates were halved (37% vs. 15%) as were the number of units transfused, length of acute hospital stay and 30 day mortality [21]. In a parallel group study [25], transfusion rates were also more than halved (70% vs. 24%) as were the number of units transfused and postoperative infection rates. Recently, the same group have reported on a randomized controlled trial of intravenous iron therapy [26]. No difference was found in transfusion rates for the trial as a whole, but prespecified subgroup analysis demonstrated a reduction in transfusion requirements for patients with subcapital fractures and those admitted with [Hb] > 12 g/dl. Overall there is a reduction in both red cell transfusion and postoperative infection of around 40%; 30-day mortality and length of stay do not appear to be altered. Laboratory data support the positive effects of i.v. iron on erythropoiesis with statistically and clinically significant increases in reticulocyte counts and iron indices. These data used non-randomized comparison groups, except for the final study. Furthermore, clinical management is different from current UK practice and guidelines, with an average time to theatre of over 4 days, compared with a UK median time of around 48 hours [27]. Recent changes to UK tariffs strongly encourage operation within 36 hours [28,29].

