### Randomization and blinding

Randomization (on a one-to-one allocation basis) is via a password-protected web-based randomization service provided by the Clinical Trials Support Unit and the sequence is not revealed until datalock. Participants are randomized within 24 hours of admission, either before or after surgery.

The treating team, research nurse collecting data and research team analyzing data will be blinded to treatment allocation. The laboratory will be blinded to treatment allocation. The patient and ward nursing staff will not be blinded, for practical reasons (Venofer is a dark brown, aqueous solution). There is no placebo.

Postoperative data collection is by a research nurse blinded to treatment allocation. The decision that a patient is medically fit for discharge is made by the multiprofessional team, when all are satisfied that the participant has no ongoing needs for acute hospital care. This team is blinded to participant allocation.

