### Statistics

Data will be analyzed by the research team in conjunction with a medical statistician, using the latest version of SPSS software. There will be no interim analysis.

The primary outcome measure, difference in mean reticulocyte count between groups in the full analysis set will be analyzed using unpaired *t* tests or Mann-Witney tests as appropriate. Differences between groups in maximal change in [Hb], serum transferrin concentration, postoperative mobility, number of units transfused and estimated costs will similarly be analyzed.

Risk ratios will be described for categorical data: the number of patients in each group with cardiovascular or infective complications; and the number of patients requiring transfusion. Descriptive statistics will be used to summarise length of stay and 30-day mortality.

Prespecified subgroup analysis will be undertaken according to admission haemoglobin concentrations ([Hb] <12 or >12 g/dl) and fracture type (sub-trochanteric, extracapsular, intracapsular, pathological).

In addition to the calculated values, confidence intervals and odds- ratios will be presented when appropriate. All clinical information including all adverse events will be presented in full. All secondary analyses will be interpreted with caution as the sample size calculation is based on the primary outcomes only. However, the level of power associated with secondary results will be investigated.

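### The overall transfusion comparison is unadjusted for admission haemoglobin and fracture type: valid, but it gives up a modest amount of precision that could be had at almost no cost (minor, optional)

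*Protocol article*

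**What the plan says.** The Statistics section fixes the method for the transfusion outcomes. For the proportion transfused: "Risk ratios will be described for categorical data", and the number of patients needing transfusion is among the data listed. For units, the t or Mann-Whitney test named for the primary outcome is carried over: "number of units transfused and estimated costs will similarly be analyzed". No covariate is named for either.

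The two baseline factors appear in one role only: "Prespecified subgroup analysis will be undertaken according to admission haemoglobin concentrations ([Hb] <12 or >12 g/dl) and fracture type". Allocation is described without stratification or minimisation: "Randomization (on a one-to-one allocation basis) is via a password-protected web-based randomization service" (Randomization and blinding).

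Elsewhere the protocol ties both factors to transfusion:

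- **Background, fracture type:** "The likelihood of transfusion is related to fracture type: subtrochanteric and trochanteric fractures have the highest transfusion rates", whether or not the patient is anaemic.
- **Background, haemoglobin:** anaemia on admission is part of the chain that leads to transfusion in one-third to two-thirds of patients.
- **Exclusion criteria:** undisplaced intracapsular fractures are left out because they are so rarely transfused.
- **Transfusion triggers:** two of the four indications use a haemoglobin threshold (10 and 8 g/dl), and a third uses haemoglobin relative to the patient's normal value.

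**The concern.** Both factors are known at baseline for every patient, since the subgroups need them. The plan uses them to divide 80 patients into small groups, which the Discussion concedes are unpowered, and not to sharpen the overall comparison. Subgroup results do not balance the overall risk ratio.

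The reticulocyte count is the primary outcome. The Discussion, however, names transfusion as the clinical outcome that iron could plausibly change, and the pilot is meant to inform a full-scale trial. Two things are at stake: some precision in the transfusion estimate, and a prespecified way to account for a visible imbalance, so that adjustment is not chosen after the data are seen.

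**Working it through.** **Inputs from the protocol.** 40 per arm (Sample size and justification); 30 to 45% anaemic on admission (Background), used here as a stand-in for haemoglobin below 12 g/dl; 38% versus 25% transfused (Background, cost paragraph).

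**The plan's own figures.** There is no power figure for transfusion to reproduce; the sample size rests on reticulocyte count, with a companion figure for transferrin receptor. The 38% and 25% serve a cost illustration, which does reproduce: (0.38 − 0.25) × 2 units × £200 = £52, less £43 for iron = £9, given as around £10. They are used below only as illustrative rates.

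**Step 1: crude precision.**

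- RR = 0.25/0.38 = 0.66.
- SE(log RR) = √[0.62/(40 × 0.38) + 0.75/(40 × 0.25)] = √(0.0408 + 0.0750) = 0.34.
- 95% CI = 0.658 × exp(±1.96 × 0.340) = 0.34 to 1.28.
- SE(risk difference) = √[(0.38 × 0.62 + 0.25 × 0.75)/40] = 0.103.
- Two-sided 5% power is about 24%; 80% power would need about 200 per arm.

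**Step 2: chance imbalance in low admission haemoglobin.** With prevalence a, the SD of the between-arm difference is √[2a(1 − a)/40] = 0.102 at a = 0.30 and 0.111 at a = 0.45. Exact binomial probabilities:

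| Imbalance of at least | Share of trials |
|---|---|
| 10 points | 39–43% |
| 15 points | 18–22% |
| 20 points | 7–9% |

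The shift in the crude risk difference is imbalance × gap in transfusion risk between strata. With an assumed gap of 20 to 40 points, a 15-point imbalance gives 0.15 × 0.20 = 3 points to 0.15 × 0.40 = 6 points, against an SE of about 10 points.

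**Step 3: gain from adjustment.** Simulation of 4,000 trials per scenario, 40 per arm, marginal rates 38% and 25%. It compares the crude RR with an RR standardised from a logistic model with continuous haemoglobin and binary fracture type (50% split assumed). All odds ratios are assumptions; the haemoglobin one is per SD decrease.

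| OR haemoglobin | OR fracture | SD(log RR), adjusted/crude | Power, crude to adjusted |
|---|---|---|---|
| 1.0 | 1.0 | 1.01 | 25% to 26% |
| 1.5 | 1.5 | 0.99 | 25% to 26% |
| 2 | 2 | 0.96 | 26% to 27% |
| 3 | 2 | 0.91 | 25% to 29% |
| 3 | 3 | 0.90 | 25% to 31% |
| 4 | 3 | 0.87 | 25% to 33% |

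The mean RR was essentially the same with and without adjustment (about 0.64 to 0.65). A second simulation with a different set-up (haemoglobin SD 1.6 g/dl, OR 0.70 to 0.45 per g/dl, fracture OR 1.5 to 2.5) took the SD of the risk difference from 0.103 to 0.101, 0.103 to 0.095 and 0.104 to 0.093: reductions of 2%, 8% and 11%.

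**Step 4: what this does to the interval.** In the strongest scenario the SE is 0.340 × 0.872 = 0.297, and the interval becomes 0.658 × exp(±1.96 × 0.297) = 0.37 to 1.18, instead of 0.34 to 1.28.

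**The case against.** The case against is strong on size. A crude risk ratio in a 1:1 randomised trial is a valid analysis. Transfusion is a secondary outcome, to be described and read with caution, in a pilot that chose reticulocytes over transfusion rate on purpose. Confidence intervals are already promised where appropriate, and an adjusted analysis may sit in an analysis plan that is not shown. The exclusions also narrow the prognostic spread. All of this stands and sets the severity. It does not remove the point, because the Statistics section states a method and a better one is available from data already collected.

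Four stronger readings are tempting, and the documents do not support them:

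- **That a reader could not tell iron from case mix.** Chance imbalance causes no systematic bias under randomisation, and the crude interval already reflects it. Results by both factors are also planned.
- **That 13 points is the planned effect.** It is the difference between two rates in a conditional cost example.
- **That 72 to 88% of anaemic patients would be transfused.** This comes from (0.55 − (1 − a) × 0.41)/a with a = 0.45 and 0.30. The 55% is from a trochanteric-fracture study with historical controls, while a is the prevalence of anaemia in hip fracture generally. The populations differ and the cut-offs may too.
- **That imbalance and unexplained variance are two separate harms.** They are one quantity. At a 55% rate the SE is √(2 × 0.55 × 0.45/40) = 11.1 points. One-SD shifts of 3.5 and 4.8 points are (3.5/11.1)² = 10% and (4.8/11.1)² = 19% of that variance, the same 10 to 19% that haemoglobin as a yes/no factor would explain.

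Nor are the two factors ignored: they define the subgroups.

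**Conclusion.** The point holds as a minor, avoidable inefficiency. The plan's transfusion comparison is sound but does not use two baseline factors that the protocol itself connects with transfusion, and its overall estimate has no prespecified way to account for an imbalance in them. An imbalance of 10 points or more in low haemoglobin would occur in about four trials in ten.

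The expected gain is a fall of about 1 to 13% in the SD of the effect estimate, with power moving from about 25% to between 26 and 33%. The possible loss is about 1% in SD. The main cause of imprecision, 40 per arm with a binary outcome, is untouched. These figures rest on assumed odds ratios, an assumed fracture split and the illustrative 38% and 25%; the protocol gives no strength for either covariate that applies to this trial's population. Severity: minor, optional.

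**What to change.** In the Statistics section, add for patients transfused a risk ratio and a risk difference, each with a 95% confidence interval, standardised from a logistic model with:

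- treatment;
- admission haemoglobin as a continuous variable;
- fracture type in two levels: extracapsular (including sub-trochanteric) versus intracapsular, with pathological fractures classed by anatomical site, since the protocol lists them as a fourth category.

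Keep to these covariates. At the illustrative rates about 40 × 0.38 + 40 × 0.25 = 25 patients would be transfused, or about 8 events for each of the three model terms. Name a penalised fit in advance for separation or too few events.

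For mean units transfused, use a linear model with the same covariates and robust standard errors. Report the crude results alongside and keep the cautious reading of secondary outcomes.

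Cost: a few lines of text, no new data and no new patients. The one downside is a model-based estimate to explain next to the crude one.

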### Sample size and justification

We propose to study a convenient sample size, with 40 participants in each group. Groups of 35 participants each would provide a statistical power of 80% for finding an absolute difference in maximum reticulocyte count of 1%, assuming a standard deviation of approximately 1.6%. This would also provide a statistical power of 80% for finding a difference in serum transferrin receptor concentration of 0.33 mg/dl. This is a conservative estimate of effect size; Garcia-Erce et al. [25] found differences of 1.75% and 0.4 mg/dl respectively. The extra ten patients are included to account for drop-outs.

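### The power statement does not follow from its inputs: 35 per arm gives about 73% power, not 80%, for a 1% difference with SD 1.6% (two-sided 5% t test)

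*Protocol article*

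**What the plan says.** The section on sample size and justification in the protocol article starts from a fixed number: "We propose to study a convenient sample size, with 40 participants in each group". It then attaches a power claim to a smaller evaluable number: "Groups of 35 participants each would provide a statistical power of 80% for finding an absolute difference in maximum reticulocyte count of 1" percentage point. The SD behind this claim is put at about 1.6%. The gap between 80 randomised and 70 evaluable is explained as a margin: "The extra ten patients are included to account for drop-outs".

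The Statistics section fixes the test as a two-sample comparison, with Mann-Whitney as the alternative to the t test: "difference in mean reticulocyte count between groups in the full analysis set will be analyzed using unpaired". Allocation is one to one (Randomization and blinding). Neither alpha nor sidedness is stated anywhere in the article.

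**The concern.** Difference, SD, number per arm and power all stand together in the sample size section, so the claim can be checked directly. A standardised difference of 0.625 with 35 per arm looks too small for 80% power at the conventional two-sided 5% level.

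If so, two things are misdescribed. The power at the number the plan expects to analyse is overstated. The ten additional patients are also not a reserve on top of an adequate 70, since they are needed to get near the target at all.

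The Statistics section says the sample size rests on the primary outcome only, and the Discussion makes the case for a full-scale trial depend on a positive result here. A reader of a null result would credit the study with more sensitivity than it has.

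**Working it through.** **Inputs**

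- Difference 1 percentage point, SD about 1.6, 35 evaluable per arm, claimed power 80% (Sample size and justification).
- 40 randomised per arm. 80 − 10 = 70 = 2 × 35 evaluable, so the allowance is 10/80 = 12.5% (same section).
- Equal allocation (Randomization and blinding); unpaired t test or Mann-Whitney (Statistics).
- Assumption, because the article is silent: two-sided alpha 0.05. Alternatives are tried below.

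**Formulas**

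Standardised difference d = 1/1.6 = 0.625. Noncentrality λ = d × √(n/2), with n per arm. Normal approximation: power = Φ(λ − 1.960). Exact t test power: the probability that a noncentral t variable with 2n − 2 degrees of freedom and noncentrality λ falls outside the two-sided 5% critical values.

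**Attempt to reproduce the stated 80% at 35 per arm**

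λ = 0.625 × √17.5 = 2.615. Normal approximation: Φ(0.655) = 74.4%. Exact t: **73.2%**. The claim is not reproduced.

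**All 40 per arm, no losses**

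λ = 0.625 × √20 = 2.795. Normal approximation: Φ(0.835) = 79.8%. Exact t: **78.8%**.

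**Number needed for 80%**

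Normal approximation: n = 2 × (1.960 + 0.842)² / 0.625² = 2 × 7.85 / 0.391 = 40.2, so 41 per arm. Exact t: 41.2, so **42 per arm**.

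**Other readings, 35 per arm, difference 1**

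| Reading | Power |
|---|---|
| Two-sided 5%, t, SD 1.6 | 73.2% |
| Two-sided 5%, t, SD 1.55 (lowest value rounding to 1.6) | 75.8% |
| Two-sided 5%, t, SD 1.65 | 70.5% |
| Two-sided 5%, Mann-Whitney on near-normal data (relative efficiency 0.955), SD 1.6 | 71.1% |
| One-sided 5% (same as two-sided 10%), t, SD 1.6 | 82.7% |
| One-sided 5%, t, SD 1.65 | 80.7% |

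With a two-sided 5% t test at 35 per arm, 80% power needs either an SD of about 1.47 or a true difference of 1.09. At 40 per arm the detectable difference is 1.01. Keeping SD 1.6 and 35 per arm, 80% would correspond to a two-sided alpha of about 0.081, which is not a conventional level.

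**The case against.** The strongest counter-argument is that the conclusion rests on an assumed test level. The abstract words the primary outcome as an increase, and the primary aim asks whether iron raises the count. A one-sided 5% test would give 82.7% at 35 per arm, so the plan would be adequate, and an SD of 1.65 would bring that to 80.7%, close to the claim. This must be disclosed. It does not displace the two-sided reading: the Statistics section analyses a difference between groups and mentions no one-sided test, and directional wording of a hoped-for result does not declare one. At the SD actually stated, the one-sided number for 80% is 33 per arm, not 35.

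The remaining points concern weight:

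- The miss at 40 per arm is marginal. It is about one point, and an SD of 1.55 would give 81.3%. It matters only because it leaves nothing for drop-outs. The full analysis set requires both an initial and a day 7 count, and the Discussion itself mentions losing participants to discharge.
- The study is a pilot of convenient size, and 1 point is called conservative against a previously observed 1.75. At 1.75 and SD 1.6, power at 35 per arm is 99.5%; at 1.25 it is 89.6%. So the trial is well powered for the larger effects, but the article claims 80% for 1 point, and that claim is wrong.
- No rule ends development after a non-significant result, and confidence intervals are planned where appropriate. The risk is over-reading a null result, not an automatic stop.

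**Conclusion.** The stated power is wrong as written. For a 1-point difference, SD 1.6 and a two-sided 5% unpaired t test, 35 analysed per arm gives 73% power, about 7 points below the claim. The type II error is 27% (1 − 0.732), not 20%. The ten extra patients restore the target only approximately, and only if nobody drops out.

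The size of the error depends on the two-sided 5% assumption. No SD that rounds to 1.6 removes it, and neither does the choice between normal approximation, t test and Mann-Whitney. Under an undeclared one-sided 5% test there would be no shortfall, but the text would still need alpha and sidedness stated and its figures aligned. The practical effect is moderate: the difference detectable with 80% power at 35 per arm moves from 1.00 to 1.09 percentage points.

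**What to change.** Rewrite the power statement in the sample size section along these lines: with two-sided alpha 0.05, SD 1.6% and a true difference of 1 percentage point, 35 analysed patients per arm give 73% power and 40 give 79%; the difference detectable with 80% power at 35 per arm is 1.09 percentage points. Describe the ten additional patients accordingly, not as a surplus over an adequate 70. If a one-sided test was intended, declare it in the Statistics section and restate the power as 83% at 35 per arm.

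This changes wording only and needs no extra patients. The cost is a less favourable stated power. Keeping 80% as a true design property would instead require 42 analysed per arm before any drop-out allowance.

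The companion claim of 80% power for a 0.33 mg/dl difference in transferrin receptor gives no SD, so it cannot be checked and no error is shown there. At 35 per arm and two-sided 5% it implies an SD of about 0.49 mg/dl (0.33 / 0.679, where 0.679 = 1.087/1.6 is the standardised difference detectable at 35 per arm). It would be sensible to confirm that value while correcting the main statement.

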**Methods/Design:**

This is a single-centre randomized controlled parallel group trial, in a British university hospital.Randomization is achieved using a website and computer-generated concealed tables. Participants are 80 patients 70 years or over with acute hip fracture undergoing operative repair. The intervention group receive three daily infusions of 200 mg iron sucrose, starting within 24 hours of admission. The control group receive standard hospital care at the discretion of the clinical team. Red cell transfusions for each group are given in accordance with standard clinical triggers. The primary outcome is an increase in mean reticulocyte count in the intervention group at day 7. Secondary outcome measures include haemoglobin concentrations, early and late transfusion rates, infectious and cardiovascular complications, mobility and 30-day mortality.

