**Discussion:**

This is a pilot study to demonstrate haematopoietic efficacy of intravenous iron in this setting. Hence, we have chosen to measure change in reticulocyte count rather than the more clinically relevant differences in haemoglobin concentration or transfusion rate. If our results are positive, the study will provide the necessary information for development of a full-scale trial of intravenous iron.

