
It is unlikely that intravenous iron, as a single intervention, will alter major outcomes, such as length of stay, mortality or readmission rates to a clinically significant degree, but it is plausible for it to have a beneficial effect on transfusion rates. However, this is only likely to happen if a significant effect on erythropoiesis occurs; hence, our choice of the absolute difference in reticulocyte count as the primary outcome of this study. We have chosen day seven as the primary time point for measuring difference in reticulocyte count. Although an effect may be seen at later times, we believe, consistent with the literature [25], that if a clinically significant effect is present, it will be observed within one week. Prolonging the observation time also risks losing participants due to discharge.

If the results of this study are positive, it will provide the necessary information for development of a full-scale trial of intravenous iron. There is an increasing awareness of the benefit of bundles of care [34] as opposed to single ‘magic bullet’ interventions [35] to improve outcomes following surgery. A full-scale trial would help to define the potential cost, resource requirement (blood products) or direct patient benefit of using intravenous iron as part of such a bundle of care. If there is a cost benefit to using intravenous iron, this could be significant: around 80,000 patients have operative fixation of hip fracture in the UK each year [36]. Conversely, if there is no benefit in the UK setting, then healthcare resources could usefully be directed elsewhere.

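### The stated 80% power belongs to the maximum reticulocyte count, but the declared primary outcome is the between-group difference at day 7

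*Protocol article*

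**What the plan says.** All references are to the protocol article.

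- **Sample size and justification.** "Groups of 35 participants each would provide a statistical power of 80" per cent for "finding an absolute difference in maximum reticulocyte count of 1%, assuming a standard deviation of approximately 1.6" per cent. Forty per arm are recruited; the ten extra patients cover drop-outs. This is the only place where a maximum reticulocyte count appears.
- **Discussion (main text).** "We have chosen day seven as the primary time point for measuring difference in reticulocyte count". The same paragraph names the absolute difference in the count as the primary outcome.
- **Abstract, Methods/Design.** "The primary outcome is an increase in mean reticulocyte count in the intervention group at day 7".
- **Abstract, Discussion.** "we have chosen to measure change in reticulocyte count".
- **Primary aims.** A rise in the count early after surgery, with no day named.
- **Statistics.** "The primary outcome measure, difference in mean reticulocyte count between groups in the full analysis set" is to be tested with an unpaired t test or its rank equivalent. No day is named, nor whether the variable is a value, a change or a maximum. The section also says that the sizing rests on the primary outcomes.
- **Definition of datasets analyzed.** The full analysis set needs both an initial and a day-7 count.
- **Laboratory analyses.** Samples are taken on admission and once daily on days 1 to 7.

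**The concern.** With daily sampling, the highest value in a patient's series need not be the day-7 value. The two can differ in mean, in spread and in the size of any treatment difference. A power figure worked out for one cannot be carried over to the other without an argument that they behave alike, and the article offers none. Its statement that the sizing is based on the primary outcomes is therefore not correct as it stands.

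Two things are at stake. First, readers cannot tell what power the declared comparison has. This matters because the result is meant to inform whether a full-scale trial is developed. Second, the day-7 value, the change from admission and the maximum can all be computed from the planned samples, and each has some support in the text. A single definition removes any doubt about which one was meant before the data were seen.

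**Working it through.** **1. The plan's own figure.** Inputs from Sample size and justification: difference δ = 1, SD σ = 1.6 (percentage points), 35 per arm. Assumed, because the article does not state it: alpha 0.05, tried two-sided and one-sided.

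n per arm = 2σ²(z_alpha + z_power)² / δ²

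- Two-sided: 2 × 2.56 × (1.960 + 0.842)² = 40.2, so 41 (42 with the t distribution).
- One-sided: 2 × 2.56 × (1.645 + 0.842)² = 31.7, so 32 (33 with the t distribution).

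Power of the unpaired t test at 35 per arm: the standard error is 1.6 × √(2/35) = 0.382, the noncentrality is 1/0.382 = 2.615, with 68 degrees of freedom.

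- Two-sided: 73.2% (normal approximation 74.4%).
- One-sided: 82.7% (normal approximation 83.4%).

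The stated 80% is not reproduced two-sided. An SD as low as 1.55, which still rounds to 1.6, gives 75.8%, and all 40 per arm give 78.8%. It is roughly consistent with a one-sided 5% test. The drop-out step is consistent: 35 / (1 − 0.125) = 40.

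**2. The day-7 count.** No day-7 SD is given, so the range below is assumed. Keeping δ = 1, 35 per arm and two-sided 5%:

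| Assumed day-7 SD | Power |
|---|---|
| 1.1 | 96% |
| 1.35 | 86% |
| 1.6 | 73% |
| 1.84 | 61% |

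The ends of the range come from two simple models of seven daily counts (200,000 simulated series each), taking 1.6 as the SD of the maximum.

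- *Normal counts, equal means and variances, correlation 0.6.* The SD of the maximum is 0.87 times the single-day SD, so the day-7 SD is 1.6 / 0.87 = 1.84.
- *Lognormal counts, correlation 0.6 on the log scale, day-7 coefficient of variation 0.4 to 0.8.* The SD of the maximum is 1.184 to 1.469 times the day-7 SD, so the day-7 SD is 1.6 / 1.184 = 1.35 down to 1.6 / 1.469 = 1.09.

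The two models move the power in opposite directions from 73%. The treatment difference may also change with the variable: at SD 1.6, a day-7 difference of 0.8 gives 54% and one of 0.6 gives 34%.

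**3. The change from admission.** If SD 1.6 is assumed at both times with correlation r, the SD of the change is 1.6 × √(2(1 − r)). For δ = 1:

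| r | SD of change | Power |
|---|---|---|
| 0.3 | 1.89 | 59% |
| 0.5 | 1.60 | 73% |
| 0.7 | 1.24 | 91% |

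The choice of variable therefore moves the power materially, even with the same patients and the same nominal effect.

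**The case against.** The strongest reply is that the intended outcome can be recovered. The Statistics section specifies an unpaired between-group test in the full analysis set, that set requires a day-7 count, and the main Discussion names day 7. Together these point to a between-arm comparison at day 7. This is right, and it limits the point to the sizing sentence and some loose wording. It does not rescue the power figure, which is still attached to the maximum.

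It can also be said that counts may peak at day 7, so that the two variables nearly coincide, and that this is a pilot with a convenience sample planned on an effect well below the 1.75% quoted from the earlier study. Both are fair. They show that the harm may be small, not that the 80% is right for day 7.

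Three stronger readings are tempting, and the article does not support them.

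- *A within-arm test that any rise after surgery would satisfy.* A reader might infer this from the abstract's wording about the intervention group. No paired or single-arm analysis is planned anywhere, and both the Statistics section and the main Discussion describe a difference between groups.
- *A maximum that drifts with length of stay.* Sampling is scheduled daily to day 7 for everyone, and a patient without a day-7 count is outside the full analysis set. At most, sporadic missed samples would matter.
- *A demonstrated loss of power.* The 61% rests on one assumed model, and another equally assumed model gives more than 80%. The gap between 61% and 80% also cannot all be charged to the mismatch, because the stated inputs reach only about 73% two-sided.

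**Conclusion.** The point holds as an inconsistency between the sizing variable and the declared primary outcome. The 80% is stated for the maximum count, while the outcome to be tested is the between-group difference at day 7. The size and direction of the error cannot be determined from the article. Under assumed day-7 SDs of 1.1% to 1.84% and a 1% difference, two-sided 5% power at 35 per arm lies between about 96% and 61%.

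Separately, the sentence does not reproduce for the maximum itself at a two-sided 5% level (about 73%). It comes near only at a one-sided 5% level (about 83%), and the article states neither alpha nor sidedness. The abstract's two phrasings and the primary aim are loose wording to be aligned, not evidence of additional planned analyses.

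**What to change.** 1. Define the primary outcome once: the between-group difference in reticulocyte count (%) at day 7. Use that wording in both abstract sections, the primary aims, Statistics, Sample size and justification, and the main Discussion. Make the maximum count a secondary outcome.
2. Analyse the day-7 count adjusted for the admission count. The full analysis set already requires that value, so no new data are needed. This also settles the choice between value and change, since with adjustment for the admission count both give the same treatment estimate.
3. Rewrite the power sentence for the day-7 count, giving the effect, the SD and its source, alpha, sidedness and the resulting power at 35 per arm. If no day-7 SD is available, say so and show power over a plausible range.

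The cost is wording and one recalculation. Recruitment can stay at 40 per arm, since the article already calls the sample one of convenience. The stated power may fall.
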